## Abstract

**Background:**

Biannual ultrasound (US)—with or without alpha-fetoprotein (AFP)—is recommended by current guidelines for the surveillance of hepatocellular carcinoma (HCC). However, the inadequate sensitivity of US has been a concern. Magnetic resonance imaging (MRI) is known to have high sensitivity in detecting hepatic malignancies, even without contrast enhancement. The purpose of our study is to compare US with noncontrast (unenhanced) MRI for HCC surveillance of high-risk patients.

**Methods/design:**

MIRACLE-HCC (usefulness of noncontrast MagnetIc Resonance imAging versus nonContrast ultrasonography for surveiLlancE of HepatoCellular Carcinoma) is a prospective, single-center, nonblinded, balanced-randomized, parallel-group study. This study was approved by our institutional review board, and informed consent will be obtained from all participating patients. All patients with compensated liver cirrhosis will undergo noncontrast US or MRI, with serum AFP testing every 6 months. If a suspicious lesion is newly detected, or if the serum AFP level is elevated in an increasing trend for two consecutive tests, dynamic contrast-enhanced imaging will be performed to confirm the diagnosis. The primary endpoints are detection rates of very early or early stage HCC, stage distribution at the initial diagnosis, and false positive referral rates, which will be compared using Fisher’s exact or chi-square tests. The study will include 416 patients in a tertiary academic medical center in South Korea.

**Discussion:**

MIRACLE-HCC is the first prospective randomized trial to compare the effectiveness of noncontrast MRI and noncontrast US in the surveillance of HCC in at-risk patients. The results of this trial will show whether noncontrast MRI surveillance is superior to noncontrast US surveillance in the early detection of HCC. The trial will also determine whether there are fewer false referrals with noncontrast MRI than with noncontrast US and, eventually, whether there is improvement in the overall survival of HCC patients.

**Trial registration:**

The date of trial registration (ClincalTrials.gov: NCT02514434) for this study is July 23, 2015. Enrollment of participants was finished in November 2017. No authors have relationships, conditions, or circumstances that present potential conflicts of interest.

**Electronic supplementary material:**

The online version of this article (10.1186/s12885-018-4827-2) contains supplementary material, which is available to authorized users.

## Background

Periodic surveillance of patients at high risk of developing hepatocellular carcinoma (HCC) is known to improve early tumor detection and overall survival [1–4]. Biannual noncontrast ultrasound (US)—with or without alpha-fetoprotein (AFP)—is recommended as a surveillance imaging modality by the current guidelines, mainly because of wide accessibility and low cost [5–8]. However, the inadequate sensitivity of US has been a concern [9], with a meta-analysis reporting a pooled sensitivity of 63% for detecting early stage HCC [10]. Moreover, the reported sensitivities of US vary widely—from 32 to 92%—in clinical practice [11, 12], demonstrating that US results can be greatly affected by several factors, including imaging protocols, equipment, patient characteristics, and operator experience [13–15].

Given the limited effectiveness of noncontrast US, other imaging modalities, such as contrast-enhanced US, contrast-enhanced computed tomography (CT), and contrast-enhanced magnetic resonance imaging (MRI), have been suggested for use in HCC surveillance [16–21]. However, contrast-enhanced US still has the limitation of being greatly influenced by patient characteristics (i.e., poor echogenic window or liver macro-nodularity) and operator experience, and CT may not be a desirable surveillance modality due to the potential risk of radiation exposure [22]. Although contrast-enhanced MRI is superior to noncontrast (unenhanced) US in detecting small tumors in patients with chronic liver disease [23], its use in HCC surveillance may be hampered by limited accessibility and high cost, as well as the issue of gadolinium-based contrast agent accumulation in human organs [24].

Even without contrast enhancement, MRI is likely to show higher sensitivity than US in detecting hepatic malignancies [25]. Furthermore, noncontrast MRI does not include dynamic sequences using contrast agents, thereby reducing the cost and scanning time, and avoiding the accumulation of gadolinium-based contrast media. We believe that these advantages could make noncontrast MRI a potential alternative to US for HCC surveillance. Therefore, we set up a prospective randomized trial to compare noncontrast US with noncontrast MRI in HCC surveillance of high-risk patients.

## Methods/design

### Study design and setting

The current trial (usefulness of noncontrast MagnetIc Resonance imAging versus nonContrast ultrasonography for surveiLlancE of HepatoCellular Carcinoma [MIRACLE-HCC]) is a prospective, single-center, nonblinded, balanced-randomized, parallel-group study. This trial is registered with ClinicalTrials.gov (identifier: NCT02514434), and the date of registration is July 23, 2015.

This study has been approved by our institutional review board (IRB) and will be conducted in accordance with the ethical principles stated in the Declaration of Helsinki and Good Clinical Practice guidelines. Any modifications to the protocol will require a formal amendment to the protocol and will be reviewed by the IRB. These modifications will be implemented only after they are approved by the IRB and notified to all participating investigators and patients. From August 2015, we recruited patients who started or had been under surveillance for HCC at the liver cancer center of Severance Hospital, a 2260-bed academic tertiary referral hospital in Seoul, South Korea. Before inclusion in the study, informed written consent has been obtained from each patient. The last patient was enrolled on November 29, 2017, and follow-up to see primary and secondary endpoints is still ongoing.

In South Korea, whose total population is approximately 51 million, the crude incidence rate of liver cancer in 2013 was 32 per 100,000 [26], and 62.7% of HCC cases are attributable to chronic hepatitis B virus infection [27]. In Korea, liver cancer is the second-most common cause of death from cancer and was estimated to be responsible for approximately 11,560 deaths in 2014 and ranked first in terms of the total economic burden during 2001–2010 [28, 29].

### Eligibility criteria

Eligible participants are adults aged 20–70 without history of liver cancer who are at risk of developing primary hepatic carcinoma (hepatitis B surface antigen positive [HBsAg+] or anti-hepatitis C virus positive [anti-HCV+] with cirrhosis, or cirrhosis from any causes), who have preserved liver function (Child-Pugh class A), and for whom the absence of a liver tumor has been confirmed clinically (no symptoms and no elevated tumor marker) and radiologically (on US, CT, or MRI) at the time of screening. Exclusion criteria are diagnosis of malignancy in the last 5 years, possible pregnancy, and severe cardiovascular, respiratory, renal, or infectious disease. The presence of cirrhosis will be determined based on the histologic or radiologic findings, including liver surface nodularity, margin blunting, segmental hypertrophy/atrophy, and findings secondary to portal hypertension (i.e., splenomegaly, esophageal or gastric varices, ascites, or reverse portal vein flow).

### Participant flow

A trained research nurse will introduce the trial to potentially eligible patients, who will be provided with detailed information about the trial. They will then be able to have an informed discussion with participating physicians, who will obtain written consent if the patients agree to participate in the trial. Enrolled participants will be randomly assigned to either abdominal US or noncontrast MRI in addition to serum AFP testing for HCC surveillance (Fig. 1). They will be evaluated by at least 10 rounds of surveillance tests at 6-month intervals (with a variation of ±1 month allowed). The first surveillance test will be performed 6 months after the most recent imaging study showing no evidence of hepatic malignancy. If a new lesion detected during US or MRI surveillance is suspected to be malignant according to the predefined criteria (see Imaging evaluation section) or if the serum AFP level is elevated in an increasing trend for two consecutive tests, dynamic contrast-enhanced CT will be performed [6, 30]. The reference value for AFP is less than 9 ng/mL at our institution. Additional dynamic liver MRI may be performed at the discretion of clinicians. If the surveillance test result is determined to be a false positive by subsequent tests, the patient will return for the next scheduled surveillance test. If a patient is confirmed as having a hepatic malignancy, the patient will receive standard treatment according to the guidelines [5–8]. We will continue follow-up of treated patients for at least 5 years to obtain and compare the overall survival rates.

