### Outcomes

The primary endpoints are detection rates of very early or early stage HCC, stage distribution at the initial diagnosis, and false positive referral rates. The detection rate is defined as the number of patients whose liver cancer is detected using a given surveillance modality divided by the total number of patients under surveillance with the modality, expressed as a percentage. Very early stage cancer is defined as a single tumor < 2 cm, and early stage cancer is defined as a single tumor < 5 cm or up to three tumors < 3 cm [7, 8]. Surveillance is considered a failure when patients are diagnosed at late (i.e., intermediate or advanced) stages. The false positive rate is defined as the number of positive tests that are eventually confirmed as negative on subsequent dynamic imaging and/or pathologic examination divided by the total number of tests in a specific surveillance modality, expressed as a percentage. The secondary endpoints are 5- and 10-year overall survival rates. We will report these long-term outcomes in separate papers.

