### Statistical analysis

Both intention-to-treat (considering all patients as randomized irrespective of the surveillance test they actually receive) and per-protocol analyses will be performed. The detection rate, stage distribution, and false positive rates will be compared between the noncontrast US and noncontrast MRI arms using the Fisher’s exact or chi-square test. To compare the variables between the two groups, we will use the independent t-test or Mann-Whitney U test for continuous variables and the chi-square or Fisher exact test for categorical variables. If necessary, we will perform logistic regression analysis to determine the independent associations between variables. Survival will be compared using the Kaplan-Meier methods with log-rank test. Cox proportional hazard regression will be performed to determine the independent associations between survival and potential explanatory variables.

Subgroup analyses will be performed. We will perform the analyses after excluding patients in whom liver cancer is diagnosed at their first MRI surveillance tests following the negative US prior to study enrollment. We will compare the tumor stages between patients diagnosed at the first tests and those diagnosed at later tests among patients undergoing noncontrast MRI surveillance. These analyses are intended to examine and exclude the possibility that the tumors already exist but are missed by the noncontrast US test prior to enrollment. In addition, we will examine the effects of the quality of the echogenic window to the liver and the parenchymal nodularity on our primary endpoints. Furthermore, we will explore the additional benefit of serum AFP testing in conjunction with noncontrast US or noncontrast MRI for the detection of early stage HCC. Two-sided *p*-values < 0.05 are considered statistically significant. All statistical analyses will be performed using the SAS 9.2 software package.

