## Discussion

Our goal is to determine whether surveillance with noncontrast MRI can further improve the overall survival of patients at high risk of developing HCC, compared with surveillance using noncontrast US. To achieve this goal, we have designed this study as a two-arm randomized trial. However, no previous study has investigated the performance of noncontrast MRI in detecting HCC patients at early stages in a surveillance setting, although one study examined the diagnostic performance of noncontrast MRI to detect and diagnose HCC in a limited cohort of patients, primarily at very early or early stages [25]. Thus, we first set our primary endpoints as detection rate of early-stage HCC and false positive rate. At long-term follow-up of the current study cohort, we may observe a significant difference in overall survival between the two arms; if this is not possible, an appropriate sample size could be calculated based on the results of current trial for a future large-scale, multicenter trial.

We will perform surveillance every 6 months using both serum AFP and imaging tests, since the combined use of noncontrast US and AFP is recommended for surveillance in many practice guidelines published in Asia, including Korea [5, 6]. Inclusion of AFP may be a confounding factor in comparing the two imaging modalities. However, it would be unethical to exclude serum AFP testing from HCC surveillance for the sake of a clinical trial because the current evidence points to noncontrast US combined with serum AFP as the most effective surveillance strategy [34]. One advantage of this study design, however, is that this trial will allow us to assess the benefit of AFP performed in addition to US or MRI in HCC surveillance, by examining the proportion of cases where early-stage HCC is detected by AFP elevation with negative US or MRI results.

We will not designate experienced radiologists specifically for our surveillance US. Instead, as is currently practiced at our institution, well-trained hepatology fellows will perform surveillance US. In real-world clinical settings, many patients receive their surveillance US examinations in local community clinics instead of tertiary care centers, often by less-experienced US operators with less-than-optimal protocols or equipment [35]. It would be unrealistic to have all surveillance US examinations performed exclusively by a limited number of highly experienced operators.

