MIRACLE-HCC is the first clinical trial to compare the effectiveness of noncontrast MRI and noncontrast US in the surveillance of HCC in at-risk patients. The results of this trial will show whether noncontrast MRI surveillance is superior to noncontrast US surveillance in the early detection of HCC, whether it results in fewer false referrals, and whether it can eventually improve the overall survival of HCC patients.

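### The protocol names two different populations for overall survival, and the only survival follow-up it specifies covers treated patients rather than everyone randomised

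*Protocol article*

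**What the plan says.** Outcomes: "The secondary endpoints are 5- and 10-year overall survival rates". It names neither a population nor a time origin.

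Participant flow sets out who is followed for survival and for how long: "We will continue follow-up of treated patients for at least 5 years to obtain and compare the overall survival rates". The sentence just before it shows how a participant comes to be treated: "If a patient is confirmed as having a hepatic malignancy, the patient will receive standard treatment according to the guidelines".

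Two summary statements name the same kind of population. The Abstract's Discussion asks "whether there is improvement in the overall survival of HCC patients", and the last paragraph of the main Discussion asks "whether it can eventually improve the overall survival of HCC patients".

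Other text points to everyone randomised. The opening of the main Discussion gives the goal as finding out whether noncontrast MRI can further "improve the overall survival of patients at high risk of developing HCC", and later in that paragraph the long-term survival comparison is described as one between the arms of the enrolled cohort. Statistical analysis begins: "Both intention-to-treat (considering all patients as randomized irrespective of the surveillance test they actually receive) and per-protocol analyses will be performed". The survival method follows in the same paragraph: "Survival will be compared using the Kaplan-Meier methods with log-rank test", again without a population or a starting point.

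**The concern.** Randomisation protects a survival comparison only if everyone randomised is in it. A patient becomes treated only after a hepatic malignancy has been confirmed, which happens after randomisation and depends in part on the test assigned. The plan itself expects the two tests to differ widely in sensitivity (60% and 90%), so the groups they select need not be alike.

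Three mechanisms follow. A more sensitive test can find more slow-growing tumours (length bias). It can find tumours that would not have affected survival (overdiagnosis). Both act through selection into the subset, whatever the starting point of the clock. If survival is also counted from diagnosis, earlier detection lengthens it even when no death is postponed (lead-time bias).

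Survival is a secondary endpoint, but the Discussion presents it as the goal of the trial. A log-rank result in diagnosed patients could not support a conclusion about patients at risk. Vital status that is not collected as the trial proceeds also becomes harder to recover.

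**Working it through.** **1. The statements side by side**

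| Place | Population implied for survival |
|---|---|
| Participant flow | Treated patients, followed at least 5 years |
| Abstract, Discussion | HCC patients |
| Discussion, last paragraph | HCC patients |
| Discussion, first paragraph | Patients at high risk; the enrolled cohort, by arm |
| Statistical analysis | As randomised (general rule), plus per-protocol |
| Outcomes | Not stated |

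The first three rows and the next two cannot all describe one comparison. No row gives a time origin.

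**2. Size of the subset**

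Inputs from Sample size: 18% HCC over 5 years, sensitivities 60% and 90%, 15% dropout, 208 per arm, 80% power, two-sided 5%.

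First, the plan's own figure. The usual two-proportion formula with pooled variance under the null gives

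n = [1.96·√(2·0.75·0.25) + 0.842·√(0.6·0.4 + 0.9·0.1)]² / 0.30² = 31.5 HCC cases per arm.

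Dividing by 0.18 × 0.85 gives 205.9 per arm, or 209.2 if n is first rounded up to 32. The stated 208 lies between them, so the 18% and 15% are used below as the plan uses them.

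- Expected HCC patients: 0.18 × 208 = 37.4 per arm (0.18 × 416 = 74.9 in all).
- After 15% dropout: 37.4 × 0.85 = 31.8 per arm.
- Detected by the assigned test at the planned sensitivities: 0.60 × 31.8 = 19.1 with US and 0.90 × 31.8 = 28.6 with MRI. Other routes to diagnosis (AFP-triggered and unscheduled CT) would add to both.
- Without HCC: 0.82 × 416 = about 341 patients.

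**3. Stated follow-up against the 10-year endpoint**

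- Patients without HCC: at least 10 rounds × 6 months = about 5 years. Nothing beyond that is stated.
- Treated patients: if diagnosed t years after randomisation, the stated minimum reaches t + 5 years. That reaches 10 years from randomisation only when t is 5 or more. Counted from diagnosis, the minimum is 5 years.
- Dropouts: efforts to obtain information on patients lost to follow-up are promised, but the example given is a patient already diagnosed with malignancy. Vital status is not mentioned.

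All of these are minimums, so longer follow-up is possible, but the text does not secure it.

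**4. What lead time alone could do, if survival runs from diagnosis**

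This is illustrative. Lead times, median survival and other-cause mortality are assumptions, not protocol figures, and there is no true benefit: death dates do not depend on arm.

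With exponential survival of median m years and a fixed lead of L years, 5-year survival from diagnosis is 2^(−5/m) in the US arm and 2^(−(5−L)/m) in the MRI arm.

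| m (years) | US arm | MRI arm, L = 0.5 | MRI arm, L = 1 |
|---|---|---|---|
| 3 | 31.5% | 35.4% | 39.7% |
| 5 | 50.0% | 53.6% | 57.4% |
| 8 | 64.8% | 67.7% | 70.7% |

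The spurious gain is about 3 to 8 percentage points.

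A simulation of the whole trial (416 patients, 18% HCC, median survival 3 or 5 years, 1% per year mortality without HCC, censoring at 10 years, 2,000 runs per setting, exponential lead capped at the diagnosis time) gave these log-rank rejection rates:

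| Mean lead before capping (years) | HCC patients from diagnosis, falsely favouring MRI (nominal 2.5%) |
|---|---|
| 0 | 1.8% to 2.4% |
| 0.5 | 6% to 9% |
| 1 | 10% to 14% |
| 2 | 18% to 31% |

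In all randomised patients from randomisation, the two-sided rate was 4.7% to 6.2% across settings (nominal 5%). Length bias and overdiagnosis were not simulated.

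**The case against.** The strongest reply is that nothing in the document restricts the survival analysis to treated patients. Participant flow describes operations. A patient with confirmed malignancy leaves the surveillance schedule, so a sentence is needed to say that follow-up goes on; everyone else stays in at least 10 rounds. On that reading, 5-year survival can be obtained for both groups apart from dropouts. The intention-to-treat sentence is not limited to particular endpoints, the Discussion speaks of the cohort and its arms, and Study design and setting says that follow-up for the secondary endpoints is continuing. The mentions of HCC patients are closing remarks rather than definitions of an estimand. A condensed article may also leave the time origin and vital-status methods to a fuller document.

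Much of this stands. A reader might infer that the plan replaces the randomised population with treated patients; the documents do not say so, and two sections point the other way. A reader might also infer that lead-time bias is built in. It is not: it depends on a time origin that is never given. Nor can a lead time in months be worked out from the 60% and 90%, because Sample size combines them with 5-year prevalence and does not describe them as per-round figures.

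What the reply does not remove is a conflict in text that is present. Participant flow gives the purpose of following treated patients as obtaining and comparing survival rates, and two summary statements name the same kind of population. An intention-to-treat rule cannot supply deaths that the follow-up arrangements do not collect, and the alternative reading does not reach 10 years.

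**Conclusion.** The point holds as an inconsistency that needs to be resolved, with moderate confidence. Participant flow, the Abstract and the closing Discussion point to treated or HCC patients; the opening Discussion and Statistical analysis point to everyone randomised.

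If the first reading were followed, the comparison would rest on about 37 patients per arm (about 32 after dropout), selected after randomisation by the assigned test and open to length bias and overdiagnosis. Lead-time bias would be added only if survival ran from diagnosis; the error rates above apply to that case alone and rest on assumed lead times and survival. Under either reading, follow-up to 10 years is not stated for the roughly 82% without HCC.

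This should be corrected because survival is the declared goal. It does not touch the primary endpoints or the 416, and survival is a secondary endpoint to be reported separately.

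**What to change.** Bring Participant flow, the Abstract and the closing Discussion into line with Statistical analysis and the opening Discussion:

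- Define overall survival as time from randomisation to death from any cause in all 416 randomised patients, by assigned arm.
- Seek vital status at 5 and 10 years for everyone, including patients without HCC and, where consent allows, dropouts.
- Label survival after HCC diagnosis as descriptive, and state that it is open to length bias, overdiagnosis and lead-time bias.

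The cost is a change of wording and a vital-status check on patients not treated for HCC. The visible survival difference will probably be smaller, since most randomised patients are not expected to develop HCC. Sample size, imaging and visits stay as they are. The article reports follow-up as still under way, so the change is easier to make now than later.

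### The protocol article contradicts itself on whose overall survival is compared: treated or HCC patients in some places, all at-risk patients by arm in others

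*Protocol article*

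**What the plan says.** Five places in the protocol article bear on the survival comparison.

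- **Participant flow.** After describing what happens once malignancy is confirmed, it says: "We will continue follow-up of treated patients for at least 5 years to obtain and compare the overall survival rates". No other sentence says from whom survival data are obtained.
- **Abstract (Discussion paragraph) and closing paragraph of the Discussion.** The trial is to show "whether there is improvement in the overall survival of HCC patients" and "whether it can eventually improve the overall survival of HCC patients". Both name HCC patients.
- **Discussion, opening paragraph.** The goal is whether MRI surveillance "can further improve the overall survival of patients at high risk of developing HCC". It adds that long-term follow-up of the cohort may show a survival difference between the two arms. This is the whole randomised population.
- **Outcomes.** "The secondary endpoints are 5- and 10-year overall survival rates". No population is attached.
- **Statistical analysis.** "Both intention-to-treat (considering all patients as randomized irrespective of the surveillance test they actually receive) and per-protocol analyses will be performed". Later in the same paragraph: "Survival will be compared using the Kaplan-Meier methods with log-rank test". Neither sentence says who enters the survival curves.

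No section states a time origin for survival.

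**The concern.** Being diagnosed with HCC happens after randomisation, and the trial exists because MRI is expected to change it: Sample size assumes sensitivities of 60% for US and 90% for MRI. Survival compared only among diagnosed or treated patients therefore compares two groups selected differently by the two arms. MRI may add slow-growing tumours, or tumours in patients who would have died of something else first (length bias). If the clock starts at diagnosis or treatment, MRI patients also gain the interval by which diagnosis was brought forward, even if every death falls on the same date (lead time).

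At stake is the long-term conclusion that the Abstract and Discussion promise. Under one reading of the text it rests on randomisation. Under the other it could favour MRI with no death prevented. Data collection is affected as well: the article reports follow-up as ongoing, and vital status that is not sought for undiagnosed patients may be hard to recover later.

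**Working it through.** **1. The plan's own figure.** No sample size is given for survival. The stated 416 concerns detection, and it reproduces as a comparison of sensitivities among HCC cases (two-sided 5%, 80% power):

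n = [1.96·√(2·0.75·0.25) + 0.842·√(0.6·0.4 + 0.9·0.1)]² / 0.30² = 31.5, rounded up to 32 cases per arm.

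32/0.18 = 177.8, and 177.8/0.85 = 209.2 per arm, about 418 in total (412 without rounding up). This does not depend on the survival population. It does show how small an HCC-only survival analysis would be: 208 × 0.18 ≈ 37 cases per arm, or about 32 after 15% dropout.

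**2. Do the passages reconcile?** The intention-to-treat sentence does not settle the matter, for three reasons.

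- Its bracket explains intention-to-treat as ignoring which test was actually received. That deals with crossover, not with who enters the survival curve.
- It cannot mean that every endpoint is computed on all randomised patients. Stage at diagnosis exists only in diagnosed patients, and the false positive rate has tests as its denominator.
- The follow-up described is not the same for everyone. All patients have at least 10 rounds six months apart, which is 10 × 0.5 = 5 years. The further follow-up of at least 5 years, stated as the source of the survival rates, is written for treated patients. A 10-year survival rate in all randomised patients is not clearly supported by that.

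**3. Size of the lead-time effect, if timed from diagnosis or treatment.** The inputs are assumptions, not figures from the article: exponential survival after diagnosis, true 5-year survival S5 of 50, 60 or 70%, lead time L of one or two surveillance rounds for every MRI patient, and no death prevented. With hazard h = −ln(S5)/5, apparent 5-year survival = exp[−h(5 − L)].

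| True S5 | L = 6 months | L = 12 months |
|---|---|---|
| 50% | 53.6% (+3.6) | 57.4% (+7.4) |
| 60% | 63.1% (+3.1) | 66.5% (+6.5) |
| 70% | 72.5% (+2.5) | 75.2% (+5.2) |

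**4. Effect on the log-rank test.** This was simulated with 208 per arm, 18% HCC, median survival after a US diagnosis of 3 or 5 years, MRI lead of 0.5 to 2 years, 1.5% yearly non-HCC mortality, 10 years of follow-up and the same death dates in both arms. Apart from the 208 and the 18%, these are assumptions.

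- HCC patients timed from diagnosis: the test falsely favours MRI in about 9 to 58% of trials (median 3 years) or 7 to 33% (median 5 years), against a nominal 2.5% in that direction.
- HCC patients timed from randomisation, with the same people diagnosed in both arms: about 5 to 7% two-sided.
- All 416 timed from randomisation: about 4 to 6% two-sided.

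The lead-time bias thus comes from the time origin. Selection on diagnosis was not modelled, so the second result does not clear an HCC-only analysis. It shows only that lead time drops out when the clock starts at randomisation.

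**The case against.** The strongest reply is that the article never says survival will be compared only in treated patients. The intention-to-treat promise is not limited to any endpoint, and the Discussion speaks of the cohort and its two arms. The Participant flow sentence can be read as keeping treated patients in follow-up once scheduled surveillance ends, alongside everyone else. The time origin is a detail that a full protocol or analysis plan may hold, and survival is secondary and deferred to separate papers.

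Much of this stands. A reader might infer that the analysis is fixed on treated patients instead of all randomised; the article does not settle that, and the finding is a contradiction. The missing time origin is not itself a fault, so every lead-time figure is conditional. What does not stand is that the general promise resolves the conflict: two statements of the aim name HCC patients, and the sentence that says how survival is obtained names treated patients.

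Two further inferences are tempting and unsupported.

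- *That patients too advanced to treat are left out.* The article says: "If a patient is confirmed as having a hepatic malignancy, the patient will receive standard treatment according to the guidelines", with no stage limit, and it undertakes to seek information on patients lost to follow-up. Selection is mainly on being diagnosed; exclusion of untreated patients is not shown.
- *That the artefact is as large as the effect sought.* That mixes denominators. Suppose late-stage shares of 40% v 10% and 5-year deaths of 20 to 30% (early) and 80 to 90% (late). The true effect among HCC patients is then 0.30 × (0.80 − 0.30) = 15 points to 0.30 × (0.90 − 0.20) = 21 points, against an artefact of 2.5 to 7.4 points in the same patients. In all randomised patients the effect is 0.18 × 15 = 2.7 to 0.18 × 21 = 3.8 points, and the artefact on that scale is about 0.5 to 1.3.

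**Conclusion.** The concern holds as a contradiction about the survival population that needs to be resolved. If the treated-patient or HCC-patient wording is followed, the comparison is conditioned on diagnosis and is not randomised; the size of that selection bias cannot be derived from the article. If it is also timed from diagnosis or treatment, lead time alone adds about 2.5 to 7.4 points to 5-year survival under the assumptions in step 3 of the working, and the log-rank test favours MRI falsely more often than its nominal level. Comparing all randomised patients from randomisation removes both problems. The point is confined to a secondary endpoint; the primary endpoints and the 416 do not change.

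**What to change.** - In Participant flow, Outcomes and Statistical analysis, state that overall survival is compared by assigned arm in all randomised patients, timed from randomisation, with vital status sought for everyone, including patients without HCC and dropouts, over the period that the 5- and 10-year rates require.
- Label any survival comparison among HCC patients as exploratory and subject to selection, lead-time and length bias.
- Align the survival wording in the Abstract and the closing paragraph of the Discussion with the goal stated at the opening of the Discussion.
- HCC-related death from randomisation could be added, but this is optional.

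Cost: mostly wording, plus collection of vital status for patients without HCC. The survival difference shown will be smaller and less precise, because about 82% of patients are not expected to develop HCC within 5 years (100% − 18%).
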